## Abstract

**Introduction::**

Community-acquired pneumonia (CAP) is the main acute complication of type 2 diabetes mellitus (T2DM) and the main cause of hospitalization for infectious diseases. Unfortunately, in the treatment of type 2 diabetes mellitus complicated with community-acquired pneumonia (T2DM-CAP), modern medicine is still faced with enormous challenges because of insulin resistance and drug-resistant bacteria. In recent decades, clinical and experimental evidence shows that Chinese herbal medicine (CHM) has a certain beneficial effect on diabetes and pneumonia. Therefore, this trial aims to assess the efficacy and safety of CHM plus western medicines for the treatment of T2DM-CAP.

**Methods::**

We propose a double-blind, placebo-controlled, randomized superiority trial.

A total of 92 participants with T2DM-CAP will be randomly allocated at a 1:1 ratio to either the experimental group, which will receive modified Ban-Xia-Xie-Xin-Decotion and basic treatment, or the control group, which will receive basic treatment only. The study duration will be 14 days. The primary outcome will be the total clinical effective rate. The secondary outcomes are traditional Chinese medicine symptom score scale, pneumonia severity index, usage time of antibiotic, time required for blood sugar to reach the required level, frequency of hypoglycemia, and chest CT. Liquid chromatograph-mass spectrometry method will be used to explore the blood metabolism profiles of the subjects, to explore the pathogenesis of T2DM-CAP and the mechanism of CHM on T2DM-CAP. Adverse events will also be evaluated.

**Discussion::**

This trial will provide evidence of the effectiveness and safety of traditional CHM in treating patients with T2DM-CAP.

**Trial registration number::**

ChiCTR2000035204

## Introduction

1

With about half a billion people affected, type 2 diabetes mellitus (T2DM) has become the leading chronic and non-communicable disease worldwide and been associated with high morbidity and mortality.^[1–2]^ In China, the prevalence of type 2 diabetes is as high as 10.4%, with more than 100 million people, accounting for about a quarter of the global total, and this number is expected to maintain an upward trend.^[1–2]^ Metabolic disorders caused by diabetes give rise to multiple organ injury. In addition, several aspects of immunity are changed in patients with diabetes. For instance, the normal role of polymorphonuclear leukocytes, leukocyte chemotaxis, adherence, and the processes of phagocytosis may be compromised.^[3–6]^ Antioxidant systems involved in bactericidal activity may also be damaged.^[7]^ The impact of these disorders on the development and prognosis of diabetes is immeasurable.

With the increase of the prevalence of diabetes, the incidence of community-acquired pneumonia (CAP) also increases significantly.^[8–9]^ CAP is a primary infectious cause of hospitalization worldwide.^[10–12]^ Previous studies have manifested that diabetes is a major risk factor for pneumonia-related hospitalizations.^[13–14]^ Individuals with DM may increase their susceptibility to pulmonary infection due to various factors, including risk of aspiration, impaired lung function, dysfunctional immunity related to the harmful effects of hyperglycaemia, and other co-existing comorbidities.^[14–15]^ Multiple studies have demonstrated that diabetics have a longer hospital stays, a higher risk of death from CAP,^[16–18]^ and a higher healthcare costs than non-diabetic patients.^[19–20]^

At present, modern medical treatment of T2DM-CAP is mainly symptomatic treatment, that is, timely use of antibiotics to control infection on the basis of controlling the level of blood glucose.^[21–22]^ Although comprehensive measures can achieve a certain effectiveness, there are still many difficulties in the treatment of the disease due to the emergence of insulin resistance and drug-resistant bacteria.^[11,23]^ Such as the repeated use of broad-spectrum antibiotics can easily induce flora imbalance and mutation strains. What is more, even if blood sugar and inflammation are controlled, there is still no significant improvement in the patient's condition. There is an urgent need for new treatment plans to improve the overall control and prognosis of T2DM-CAP and reduce medical costs.

Considering the risk of antibiotic resistance and insulin resistance, the combined use of drugs is gradually becoming more popular. Chinese herbal medicine (CHM) has been used for thousands of years for treating pneumonia or diabetes. In recent decades, evidence from both clinicians and patients suggests that CHM has some beneficial effect on CAP^[24–25]^ and diabetes.^[26–27]^ Our research group has been engaged in diabetes research for nearly 20 years. Ban-Xia-Xie-Xin-Decotion (BXXXD) is composed of 7 herbs and has been proved to have good treatment effects both in clinic and experimental studies.^[28–30]^ Modern pharmacological studies have shown that the formula has multiple effects such as anti-inflammatory, antioxidation, antitussive, and immunomodulatory.^[31–33]^ Nevertheless, the effects of modified BXXXD on the clinical prognosis of CAP patients with diabetes remain unclear. Thus, this trial aims to assess the efficacy and safety of modified BXXXD plus western medicines for the treatment of T2DM-CAP. In addition, Blood metabolism profiles of participants by liquid chromatograph-mass spectrometer method will be measured to explore the pathogenesis of T2DM-CAP and the mechanism of drug action.

## Methods/design

2

### Design

2.1

This study is a randomized, double-blind, placebo-controlled clinical trial. This trial has been registered with the Chinese Clinical Trial Registry. After obtaining written informed consent, 92 eligible participants will be randomly assigned to the experimental group or control group in a 1:1 ratio. The 2 groups will then undergo a 2-week treatment period. The trial aims to investigate the additional benefits and safety of CHM plus western medicines compared with western medicine treatment only of T2DM-CAP, and to explore the mechanism in light of Metabonomics. The study will comply with the Standard Protocol Items: Recommendations for Interventional Trials 2013 statement (see Fig. 1 for the Standard Protocol Items: Recommendations for Interventional Trials figure of enrollment, interventions, and assessments). The research flow chart is illustrated in Figure 2.

**Figure 1 F1:**
[figure not shown]
Spirit figure of enrollment, interventions, and assessments.^[1]^ Laboratory examination: including white blood cell count, percentage of neutrophils, C-reactive protein and procalcitonin.^[2]^ Auxiliary examination: blood, urine, feces, electrocardiogram, kidney, and liver function.

**Figure 2 F2:**
[figure not shown]
Flowchart of the study design. CAP = community-acquired pneumonia, T2DM = type 2 diabetes mellitus, TCM = traditional Chinese medicine.

### Ethics approval

2.2

The final amendments (version: July 31, 2020) and the consent form have been reviewed and approved by the China Ethics Committee of Registering Clinical Trials (Approval No. ChiMCTR2000003540). The study will abide by the Declaration of Helsinki (Edinburgh 2000 version).

### Recruitment

2.3

All patients with T2DM-CAP at endocrinology department and respiratory department in hospital of Chengdu University of Traditional Chinese Medicine (TCM) (Chengdu, China) will be screened and enrolled. Prior to enrollment, subjects will be informed about the detailed explanation of the clinical study, including the purpose, scheduling, and possible benefits and risks. All eligible participants will be required to sign an informed written consent before the start of the study process. Patient recruitment starts in August 2020 and is planned to be completed in August 2021.

### Sample size

2.4

Sample size calculations are based on the primary outcome (the clinical effective rate at 2 weeks). According to the previous literature,^[34]^ we assumed the clinical effective rate of 73% in the control group and 93% in the experimental group over 14 days. Thus, a sample size of 82 patients is needed to achieve a statistical power of 80% (single-sided type-1 error of 5% in both scenarios). Assuming that 10% of patients are likely to be lost during follow-up, a total of 92 patients will be enrolled.

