### Statistical analysis

3.8

Statistical analysis will be performed at the Sichuan evidence-based Medicine Center of TCM using Statistical Package for the Social Sciences version 22.0 (SPSS 22.0, Chicago, IL). Intention-to-treat and per protocol sets are applied to analyse the efficacy of modified BXXXD. A safety analysis set is used to assess the safety of the study. Missing values are estimated using the principle of the last observation carried forward, with the data from the last study follow-up used as the final results.

Categorical data are tabulated with frequencies or percentages, and continuous data are reported as median or mean ± standard deviation. For the sociodemographic data and baseline variables are conducted using analysis of variance and Chi-squared test. To compare the variables of the same group before and after treatment, a paired *t*test is used. Repeated measures analysis of variance is used to compare the differences among the 2 groups. All statistical tests are bilateral tests and *P* values < .05 is regarded as statistical significance.

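### The trial is sized at a one-sided 5% error but tested two-sided at 5%, so the stated 80% power is really about 70%

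*Protocol article*

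**What the plan says.** The sample size section (2.4) bases the calculation on the clinical effective rate at two weeks: "we assumed the clinical effective rate of 73% in the control group and 93% in the experimental group over 14 days". From this it concludes that "a sample size of 82 patients is needed to achieve a statistical power of 80% (single-sided type-1 error of 5% in both scenarios"). It then allows for loss: "Assuming that 10% of patients are likely to be lost during follow-up, a total of 92 patients will be enrolled". Allocation is 1:1 (section 2.1).

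The statistical analysis section (3.8) sets the decision rule for the whole trial. It states "All statistical tests are bilateral tests", and that P "values < .05 is regarded as statistical significance". The primary outcome is not exempted, and no one-sided test is declared anywhere in the article.

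**The concern.** The protocol fixes sidedness twice, in opposite ways. A two-sided test at 5% puts 2.5% in the favourable direction, so it asks for stronger evidence than the one-sided 5% test behind the sample size. With the same number of patients, power must fall.

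Two things are at stake. First, the 80% figure is the only justification given for the number enrolled, and a non-significant result would be read against a power that the design does not have. Second, the decision rule for the primary outcome is left open. A favourable result with a two-sided P between .05 and .10 is significant by the error rate in section 2.4 and not significant by the rule in section 3.8. Which reading applies should not be decided after the data are seen.

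**Working it through.** **Inputs.** Control rate 0.73, experimental rate 0.93, power 80%, one-sided 5% error, 10% loss (all section 2.4); 1:1 allocation (section 2.1); two-sided tests with P < .05 (section 3.8). Normal quantiles: 1.645 (one-sided 5%), 1.960 (two-sided 5%), 0.842 (80% power).

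**Step 1: reproduce the plan's figure.** The unpooled formula for two proportions is

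n per arm = (z_α + z_β)² × [p₁(1 − p₁) + p₂(1 − p₂)] / (p₂ − p₁)²

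The variance term is 0.73 × 0.27 + 0.93 × 0.07 = 0.1971 + 0.0651 = 0.2622. At one-sided 5%:

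(1.645 + 0.842)² × 0.2622 / 0.20² = 40.5, so 41 per arm and 82 in total.

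Allowing for loss, 82 / 0.90 = 91.1, so 92. Both stated figures are reproduced.

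**Step 2: check that the one-sided level was really used.** Total N for 80% power by other common methods:

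| Method | One-sided 5% | Two-sided 5% |
|---|---|---|
| Unpooled | 82 | 104 |
| Pooled | 86 | 110 |
| Arcsine | 80 | 102 |
| Pooled, continuity-corrected | 106 | 128 |

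Exact enumeration of the uncorrected one-sided chi-square test also leads to 41 per arm (79.7% at 40, 80.8% at 41), so the formula behind the 82 cannot be inferred with certainty. What is clear is that no two-sided version in the table gives 82. The word for one-sided in section 2.4 is not a slip of the pen.

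**Step 3: power under the test in section 3.8.** With the unpooled formula and 41 per arm, the standard error is √(0.2622 / 41) = 0.0800, and 0.20 / 0.0800 = 2.50. Power is Φ(2.50 − 1.960) = Φ(0.54), which is 70.6% without intermediate rounding. The same calculation at the one-sided level is Φ(2.50 − 1.645) = 80.4%.

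| Method, two-sided 5% | 41 per arm (82 evaluable) | 46 per arm (all 92) |
|---|---|---|
| Pooled | 68.0% | 73.1% |
| Unpooled | 70.6% | 75.5% |
| Arcsine | 71.3% | 76.2% |
| Exact, uncorrected chi-square | 71.4% | 76.7% |
| Exact, Fisher | 61.2% | 65.8% |

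**Step 4: size needed for 80% at two-sided 5%.** Unpooled: (1.960 + 0.842)² × 0.2622 / 0.04 = 51.4, so 52 per arm and 104 in total. Pooled: 54.2, so 55 per arm and 110 in total. The exact chi-square test first reaches 80% at 50 per arm (80.3%), falls to 79.3% at 51 and returns to 80.2% at 52, because the test is discrete. About 104 to 110 evaluable is a safe statement. With 10% loss, 104 / 0.90 = 115.6 and 110 / 0.90 = 122.2, so 116 to 123 enrolled.

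**The case against.** The best defence is that section 2.4 contains no arithmetic error: on its own inputs, 82 and 92 are right. That stands. The fault is an inconsistency between two sections, and the 80% is wrong only in relation to the test the protocol prescribes.

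A one-sided primary test can also be legitimate if it is declared and justified in advance. Section 3.8 rules it out as written, so this is a possible repair and not a reading of the current text.

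The size of the shortfall depends on choices the article does not settle. Section 3.8 includes an intention-to-treat set with last observation carried forward. If that keeps all 92 patients at the assumed rates, power is 73% to 77% and not 68% to 71%. The article names the chi-square test only for baseline data, and Fisher's exact test would give about 61% at 82 evaluable. These points widen the range, but none of these cases reaches 80%.

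Finally, the two-sided test is the stricter one, so it does not inflate the type I error or bias any estimate, and the discussion concedes a small sample and calls the evidence preliminary. That is true, but the general caveat does not correct the specific 80% claim.

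**Conclusion.** The concern holds. Sections 2.4 and 3.8 contradict each other on sidedness, and nothing else in the article reconciles them. Under the two-sided 5% rule, power is about 70% with the 82 evaluable patients to whom the 80% claim applies, a shortfall of 9 to 12 percentage points. The type II error is 29% to 32% where the protocol implies 20%. With no loss at all, power is about 75%.

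These figures assume true rates of 73% and 93%, equal arms, and an uncorrected chi-square or equivalent z test. A smaller true difference between the arms, or a more conservative test, would generally lower them further. The phrase about both scenarios in section 2.4 does not resolve the conflict, because only one pair of rates is given.

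**What to change.** Keep the two-sided 5% test and the 92 patients, and rewrite the power sentence in section 2.4. It should say that, at 73% versus 93% and two-sided 5%, power is about 70% with 82 evaluable patients and about 75% if all 92 are analysed. It should name the formula, and drop both the one-sided wording and the reference to two scenarios. The cost is one sentence and a less favourable power figure; no patients are added.

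Two other repairs are open to the sponsor. Restoring 80% power under the two-sided test takes 116 to 123 enrolled, which is 24 to 31 more than planned. Alternatively, section 3.8 could declare a one-sided 5% primary test with a justification, but that doubles the false-positive rate in the favourable direction from 2.5% to 5%. Whichever is chosen, the two sections must agree before unblinding.

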#### Primary outcome

3.3.1

Disease outcomes include cure, significant effect, effective, and ineffective. The main result is the total clinical effectiveness after treatment (day 14) of the 2 groups, that is, the sum of cure rate, apparent efficiency and effective.

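### The stated 80% power fits an analysis of about 82 completers; intention-to-treat power depends on how lost patients are scored, and is about 65-75% if they show no treatment difference

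*Protocol article*

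**What the plan says.** Section 2.4 (Sample size) sets the rates: "we assumed the clinical effective rate of 73% in the control group and 93% in the experimental group over 14 days". From these it concludes that "a sample size of 82 patients is needed to achieve a statistical power of 80" per cent, at a "single-sided type-1 error of 5% in both scenarios". It then adds the allowance for loss: "Assuming that 10% of patients are likely to be lost during follow-up, a total of 92 patients will be enrolled". Section 2.1 (Design) fixes equal allocation, so 92 means 46 per arm.

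Section 3.8 (Statistical analysis) states: "Intention-to-treat and per protocol sets are applied to analyse the efficacy of modified BXXXD". Neither set is named as primary. On missing data it says: "Missing values are estimated using the principle of the last observation carried forward".

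Section 3.3.1 (Primary outcome) times the endpoint: "The main result is the total clinical effectiveness after treatment (day 14) of the 2 groups". Section 3.3.2 lists earlier visits for several secondary outcomes, but the article lists no effectiveness rating before day 14.

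**The concern.** Dividing by one minus the loss rate is the right allowance when lost patients leave the analysis and the rest show the assumed rates. It replaces the missing numbers and nothing else. An ITT analysis with carried-forward values does not let lost patients leave. They stay in each arm's denominator with whatever status was last recorded. If that status shows less than the full difference between arms, the difference tested is smaller than 20 points, and the ten added patients do not necessarily make up for it.

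Section 2.4 applies 73% and 93% without any adjustment for loss, so its 80% belongs to an analysis of about 82 completers. What is at stake is how a null result would be read. A non-significant ITT comparison in this superiority trial would be judged against a claimed 80% power that this comparison may not have.

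**Working it through.** **Inputs.** Rates 0.73 and 0.93, one-sided alpha 0.05, power 0.80, 82 patients before loss, 10% loss and 92 enrolled (section 2.4); 1:1 allocation (section 2.1); lost patients kept by carrying forward (section 3.8). The response of lost patients is not in the article and is varied below. Loss is taken as 10% in each arm.

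**Step 1: reproduce the plan.** Two proportions, unpooled variance:

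n per arm = [p1(1−p1) + p2(1−p2)] × (1.645 + 0.842)² / (p2−p1)²

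= (0.1971 + 0.0651) × 6.18 / 0.04 = 40.5, raised to 41, or 82 in total.

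Power = Φ{(p2−p1) / √([p1(1−p1) + p2(1−p2)]/n) − 1.645}. At 41 per arm: 0.20/0.0800 = 2.501, and Φ(2.501 − 1.645) = Φ(0.856) = 80.4%.

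Loss: 82/0.9 = 91.1, raised to 92. Both stated figures reproduce, which identifies the method and shows that loss enters only through the head count.

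**Step 2: ITT power at 46 per arm.** The rate in each arm becomes 0.9 × (completer rate) + 0.1 × (rate among lost patients). For example, if lost patients count as ineffective: 0.9 × 0.73 = 0.657 and 0.9 × 0.93 = 0.837. The difference is 0.18, the standard error √(0.3618/46) = 0.0887, and Φ(2.030 − 1.645) = Φ(0.385) = 65.0%. The other rows use the same formula.

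| Assumption for the lost 10% | Control | Experimental | Power, one-sided 5% |
|---|---|---|---|
| Ineffective in both arms | 65.7% | 83.7% | 65.0% |
| Half effective in both arms | 70.7% | 88.7% | 71.1% |
| Control rate (73%) in both arms | 73.0% | 91.0% | 74.7% |
| Carried-forward rates are 50% of final rates | 69.35% | 88.35% | 74.2% |
| Carried-forward rates are 70% of final rates | 70.81% | 90.21% | 78.2% |
| Experimental patients keep half the effect | 73.0% | 92.0% | 79.7% |
| All effective in both arms | 75.7% | 93.7% | 79.7% |
| Experimental patients keep 60% of the effect | 73.0% | 92.2% | 80.7% |
| Carried-forward rates are 90% of final rates | 72.27% | 92.07% | 82.2% |
| Experimental patients keep the full effect | 73.0% | 93.0% | 84.2% |

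**Step 3: check with a pooled variance.** The four main cases become 63.6% (ineffective), 73.2% (control rate), 78.2% (half the effect) and 82.7% (full effect). The pattern does not depend on the formula.

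**Step 4: which rows are plausible.** If no effectiveness rating before day 14 exists, carrying forward may amount to carrying baseline status, which is the ineffective row. If a grade can be built from day 4 or day 8 data, some of the effect would be kept and a row further down applies. Section 2.10 also withdraws patients for severe deterioration, severe adverse reactions or low intake. If their later data are missing, they are unlikely to show the full benefit.

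**The case against.** The arithmetic in section 2.4 is correct: 82 and 92 both reproduce. Dividing by one minus the loss rate is the usual allowance, and section 2.4 does not say that its 80% is the power of the ITT comparison. Section 3.8 also lists a per-protocol set and names neither set as primary, a choice that may sit in an analysis plan not shown here. All of this stands, so the point concerns which analysis the 80% describes, not a calculation error.

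A reader might infer that ITT power simply is 65-75%. The article does not support that. The range requires lost patients to show no difference between arms and to respond at a rate between zero and the control rate, and the article gives no such rate.

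A reader might also infer that 80% is reached only if lost patients show the full difference. The table contradicts this: keeping half the effect gives 79.7%, and keeping 60% gives 80.7%.

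Nor does the common rule of dividing by the square of 0.9 give a sound replacement size. 82/0.81 = 101.2, or 102 in total; at 51 per arm, power is about 69% with lost patients ineffective and about 78% at the control rate.

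The 73% and 93% come from a cited source that cannot be checked here. If those rates already count dropouts, diluting them again would overstate the loss of power. Section 2.4 does, however, apply them unchanged to the number left after loss, and so treats them as completer rates.

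Finally, section 3.8 makes all tests two-sided. At two-sided 5%, 41 per arm gives Φ(2.501 − 1.960) = about 71%, so even the completer figure of 80% holds only at the one-sided level. That conflict is a separate matter, but it has to be settled before any figure is restated.

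**Conclusion.** The concern holds as a mismatch between the loss allowance and one of the two efficacy analyses. The stated 80% is right for about 82 completers at one-sided 5%. For the ITT set of 92, power runs from about 65% to 84% over the assumptions examined. It is about 65-75% if lost patients show no treatment difference and respond at no more than the control rate, and about 80% or more if lost experimental patients keep at least half of the effect.

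This rests on equal 10% loss in both arms, on 73% and 93% being completer rates, on the plan's unpooled formula and on its one-sided 5%. The response of lost patients is an assumption throughout. The absence of a listed effectiveness rating before day 14 makes the lower end plausible but does not establish it.

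**What to change.** Keep 92. In section 2.4, state that 80% power applies to the analysis of about 82 completers, and add the ITT power under an explicit assumption about lost patients. If they are assumed to show no treatment difference, that is about 65-75% at one-sided 5%, according to whether they count as ineffective or respond at the control rate.

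First reconcile the one-sided alpha in section 2.4 with the two-sided tests in section 3.8, and calculate both the completer and the ITT figures at the alpha adopted.

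The cost is a few sentences and a less favourable stated power. No patients are added and the conduct of the trial does not change.
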